## Abstract

**Background:**

Prolonged disorders of consciousness (pDoC) resulting from intracerebral hemorrhage (ICH) significantly impair patients’ quality of life. This study aims to investigate the therapeutic effects of transcranial direct current stimulation (tDCS) combined with median nerve stimulation (MNS) in patients with pDoC 3–12 months post-ICH.

**Methods:**

This prospective, double-blind, randomized controlled trial will enroll 138 eligible patients with pDoC following ICH. Participants will be randomly assigned to three groups of 27 each: (1) tDCS + MNS, (2) sham tDCS + MNS, and (3) tDCS + sham MNS. The intervention will last for 4 weeks, followed by a 6-month follow-up period. The primary outcome measure is the change in the Coma Recovery Scale-Revised (CRS-R) scores. Secondary outcomes include electrophysiological and neuroimaging data. Assessments will be conducted at baseline, after 4 weeks of treatment, and at 2 weeks, 4 weeks, 12 weeks, and 24 weeks post-intervention.

**Discussion:**

The strengths of this study include the combined intervention approach of tDCS and MNS, as well as comprehensive outcome measures. This intervention may promote consciousness recovery through multiple mechanisms, including enhanced neuroplasticity and modulation of brain networks. This study aims to provide a novel approach for consciousness-promoting treatment in pDoC, potentially improving patient prognosis and quality of life.

**Clinical trial registration:**

https://www.chictr.org.cn/showproj.html?proj=203618, identifier ChiCTR2300075190.

## Introduction

Prolonged disorders of consciousness (pDoC)refer to a state of impaired consciousness lasting more than 28 days after brain injury, primarily encompassing vegetative state (VS)/unresponsive wakefulness syndrome (UWS) and minimally conscious state (MCS) (1). MCS can be further divided into MCS + and MCS- depending on specific behavioral signs (2), with MCS + patients showing command following, intelligible verbalization, or gestural or verbal yes/no responses, while MCS- patients only show non-reflex movements such as visual pursuit, localization of noxious stimulation, or appropriate affective responses. MCS- is characterized by the absence of language function despite the presence of these non-reflexive behaviors. pDoC can result from various aetiologies, including traumatic brain injury, intracerebral hemorrhage (ICH), ischemia, anoxia, and other mixed causes. In the context of this study, we define consciousness as the clinical measurable capacity for awareness of self and environment, which can be operationalized and assessed through standardized tools like the CRS-R. This operational definition focuses on observable behavioral responses indicating levels of wakefulness and awareness, which serves our clinical research purpose. We acknowledge that this definition may be distinguished from other broader perspectives that explore the wider implications of consciousness for human development and evolution. For instance, Kotchoubey (3) proposed that human consciousness originates at the intersection of communication, play, and tool use. Likewise, Dresp-Langley (4) suggested that consciousness extends beyond neural domains to facilitate adaptation to unprecedented challenges. This study specifically focuses on pDoC following ICH. Patients with pDoC exhibit severe impairments in consciousness level and cognitive function, significantly affecting their quality of life and imposing a substantial burden on families and society (5). Recent epidemiological studies indicate that the incidence of VS/UWS is approximately 5–10% among patients with severe brain injuries (6). The overall incidence of pDoC (including both VS/UWS and MCS) among ICH survivors is estimated to be higher (7). In China, with an estimated 400,000–600,000 new cases of ICH annually, potentially leading to 20,000–60,000 cases of pDoC, research into effective consciousness-promoting methods for pDoC holds significant societal value (8).

Current treatments for pDoC include pharmacological interventions (e.g., amantadine, zolpidem), physical therapy, sensory stimulation, and neuromodulation techniques (9). However, these approaches have limitations: pharmacological treatments often yield inconsistent results with high individual variability and potential severe adverse effects (10); traditional rehabilitation therapies progress slowly with limited efficacy (11); while invasive neuromodulation techniques (such as deep brain stimulation) show promise, they carry higher risks and are not suitable for widespread application (12).

Given the limitations of existing treatments, non-invasive neuromodulation techniques have garnered considerable attention in recent years, particularly the combined application of transcranial direct current stimulation (tDCS) and median nerve stimulation (MNS). tDCS applies weak direct current through scalp electrodes, modulating cortical excitability and promoting neuroplasticity (13). Thibaut et al. (14) found that a single session of tDCS can temporarily improve behavioral responses in MCS patients, while Wu et al. (15) demonstrated that repeated tDCS might enhance consciousness levels in patients with disorders of consciousness (DoC). MNS influences central nervous system function through peripheral nerve stimulation (16). Zhang et al. (17) discovered that MNS can increase electroencephalogram complexity in VS/UWS patients, and Raichur et al. (18) explored the combined application of tDCS and MNS in DoC patients with traumatic brain injury, with preliminary results suggesting that combined therapy may be superior to monotherapy. The combination of these two techniques offers advantages of high safety, ease of operation, and relatively low cost, potentially producing synergistic effects through different mechanisms of action (16).

However, current research on combined tDCS and MNS treatment for pDoC patients has limitations: existing studies have primarily focused on patients with traumatic brain injury, with fewer studies on pDoC patients following ICH (19); most studies have small sample sizes and short follow-up periods, making it difficult to evaluate long-term treatment effects (19, 20). Furthermore, recent literature suggests that the period of 3–12 months post-ICH is critical for neurological recovery, indicating that patients within this time window may have greater potential to respond to neuromodulation therapy (21).

Based on these considerations, we have designed a prospective randomized controlled trial at the Rehabilitation Department of Guangdong Sanjiu Brain Hospital to investigate the therapeutic effects of combined tDCS and MNS in pDoC patients following ICH. This study will focus on patients 3–12 months post-ICH and include a 6-month follow-up period to comprehensively assess the long-term efficacy, safety, and mechanisms of action of this combined treatment approach. This research aims to provide more reliable and comprehensive scientific evidence for the clinical management of pDoC following ICH.

## Study design

This is a prospective, single-center, three-arm parallel randomized controlled trial. Patients will be randomly assigned to three groups: (1) tDCS+MNS group: receiving real tDCS and MNS treatment; (2) Sham tDCS+MNS group: receiving sham tDCS and real MNS treatment; (3) tDCS+Sham MNS group: receiving real tDCS and sham MNS. Each group will consist of 27 patients, with treatment lasting for 4 weeks (22).

Randomization will be implemented using a web-based central randomization system, developed by an independent statistician using the “blockrand” package in R software (version 4.1.0) (23). We will employ a stratified randomization strategy to ensure balanced baseline characteristics across groups. Randomization will be stratified by age (≤50 years/>50 years) and baseline consciousness level (vegetative state/minimally conscious state) (9). The allocation ratio will be 1:1:1, using variable block sizes (4 or 6) to enhance allocation unpredictability. To ensure allocation concealment, the randomization sequence will be stored in the central randomization system, and the study coordinator will only obtain the allocation result through this system after the patient has completed all baseline assessments and confirmed eligibility. The system will send the allocation result to the therapist responsible for implementing the intervention via encrypted email.

This study employs a triple-blind design, where patients, outcome assessors, and data analysts will be blinded to treatment allocation. Patients, outcome assessors, and data analysts will be blinded to treatment allocation. To achieve this, we will adopt the following strategies: (1) All patients will receive identical electrode placement and stimulation duration, regardless of real or sham stimulation. (2) tDCS and MNS devices will be pre-programmed to provide either real or sham stimulation. These devices will be identical in appearance and operated by technicians not involved in patient assessment. (3) Sham stimulation will deliver a brief current for the initial 30 s, mimicking the sensation of real stimulation, before gradually ramping down to zero. This sham tDCS protocol has been validated in previous studies with both healthy participants and patients with disorders of consciousness, showing that participants cannot reliably distinguish between real and sham stimulation (20). (4) All research personnel will receive standardized training to ensure consistency in treatment and assessment procedures. To maintain blinding, we will implement the following measures: (1) All research personnel and participants will be instructed not to discuss treatment details during the study. (2) The effectiveness of blinding will be regularly assessed by asking assessors to guess the type of treatment they evaluated. For patients who regain communication ability during the study (emerging from MCS), we will also ask them to guess which treatment they received, but this will not be possible for patients who remain in pDoC throughout the study. (3) During the data analysis phase, treatment groups will be coded (e.g., A, B, C) until all analyses are completed. Unblinding will only occur in the event of serious adverse events or when patient safety considerations necessitate it. The unblinding procedure will be executed by an independent safety monitoring committee not involved in daily patient management.

Patient recruitment is scheduled to begin on October 1, 2024, with all follow-ups expected to be completed by September 31, 2025. The primary outcome measure (CRS-R scores) will be assessed at baseline, after 4 weeks of treatment, and at 2 weeks, 4 weeks, 12 weeks, and 24 weeks post-intervention (24).

All procedures will strictly follow the SPIRIT (Standard Protocol Items: Recommendations for Interventional Trials) guidelines and checklist, as well as the consolidated standards of reporting trials guidelines (Figure 1).

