#### Follow-up retention strategy

To minimize attrition during the 6-month follow-up period, we will implement several retention strategies: (1) Assigning a dedicated research coordinator to maintain regular contact with participants’ families/caregivers; (2) Providing flexible scheduling options for follow-up assessments, including the possibility of home visits when appropriate; (3) Reimbursing transportation expenses for hospital visits; (4) Implementing telephone or video follow-ups for interim check-ins between scheduled assessments; (5) Providing clear information about the importance of complete follow-up data; (6) Sending reminder communications before each scheduled assessment; and (7) Collecting multiple contact methods (phone, email, alternative contacts) to maintain communication if primary contact methods fail. Additionally, we will monitor reasons for withdrawal and address any systematic issues that emerge during the trial.

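### Each patient's allocation goes to the study coordinator, who has no stated need for it, so past assignments accumulate at one site and later ones become partly predictable

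*Protocol article*

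**What the plan says.** All of the following is in the protocol article.

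- **Release of allocation (Study design).** The list is held in a central web system. On its release the article says: "the study coordinator will only obtain the allocation result through this system after the patient has completed all baseline assessments and confirmed eligibility". A second recipient follows in the next sentence: "The system will send the allocation result to the therapist responsible for implementing the intervention via encrypted email".
- **Scheme (Study design).** The trial has one centre and three arms. "Randomization will be stratified by age (≤50 years/>50 years) and baseline consciousness level (vegetative state/minimally conscious state"), which makes four strata. "The allocation ratio will be 1:1:1, using variable block sizes (4 or 6) to enhance allocation unpredictability".
- **Delivery (Study design).** "tDCS and MNS devices will be pre-programmed to provide either real or sham stimulation", and the devices are "operated by technicians not involved in patient assessment".
- **Who is blind (Study design).** The article states that "patients, outcome assessors, and data analysts will be blinded to treatment allocation". The coordinator, the therapist and the technicians are not on that list. Coding of the groups by letter is mentioned only for the data analysis phase. All research staff are told to keep silent about treatment.
- **Family contact (Follow-up retention strategy).** The first measure is "Assigning a dedicated research coordinator to maintain regular contact with" families and caregivers. The section does not say whether this is the coordinator who obtains the allocation.

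**The concern.** Allocation concealment has two parts: the current assignment must be hidden until the patient is irrevocably entered, and future assignments must not be inferable from past ones. The article secures the first. It weakens the second by giving a site role the result for every patient. With small permuted blocks in four strata, that running record tells its holder which arm is likely to come next. Variable block sizes are meant to prevent this, but they work best when past assignments are also hidden.

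If that person, or someone they talk to, influences entry, a borderline decision or the timing of consent could follow the expected arm. Some exclusion criteria leave room for judgement, such as whether spasticity is severe or whether the patient will be able to complete treatment and follow-up. If that person also deals with families, visits could be pursued or events asked about differently by arm. Caregiver reports are one source of adverse-event information (Study safety).

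**Working it through.** The plan states no figure for predictability, so there is nothing to reproduce. The check has three steps.

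**1. Inputs.** Three arms at 1:1:1, four strata, one centre, and block sizes 4 or 6 (Study design). The total is 81 (Sample size); the Abstract also gives 138. Assumption: the strata are equally likely, so about 81 / 4 ≈ 20 patients each.

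**2. Block sizes.** 6 / 3 = 2 per arm, so a block of 6 balances. 4 = 3 + 1, so a block of 4 leaves one spare slot and cannot be 1:1:1. The scheme as printed therefore cannot be simulated without an assumption, and a range is needed.

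**3. Chance of guessing the next arm.** The guesser knows the past allocations in the stratum and names the arm with the most slots left, which is the arm least used so far. At each position the chance of being right is the largest remaining count divided by the slots remaining. For a block of 6, averaged over all possible histories:

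| Position | 1 | 2 | 3 | 4 | 5 | 6 |
|---|---|---|---|---|---|---|
| P(correct) | 1/3 | 2/5 | 1/2 | 8/15 | 3/5 | 1 |
| P(known for certain) | 0 | 0 | 0 | 0 | 1/5 | 1 |

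- Sum of P(correct) over one block: 10/30 + 12/30 + 15/30 + 16/30 + 18/30 + 30/30 = 101/30 = 3.367.
- A stratum of 20 is three full blocks plus two patients: (3 × 3.367 + 1/3 + 2/5) / 20 = 10.83 / 20 = 54.2% correct.
- Known for certain: 3 × 1.2 / 20 = 18%.

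Other schemes were simulated. One method uses strata of 20 and a guesser who only counts arms. The other uses 81 patients spread at random over four strata and a guesser who knows the possible block sizes.

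| Assumed blocks | Counting only | Knowing the sizes | Known for certain |
|---|---|---|---|
| 4 or 6, spare slot of the 4 drawn at random | 50% | not run | not run |
| 6 only | 54% | 54.5% | 17.6% |
| 3 or 6 | 56% | 56.4% | 7.9% |
| 6 or 9 | not run | 52.6% | 4.5% |
| 12 or 18 (if 4 and 6 are counts per arm) | 47% | 46.9% | 2.4% |
| Arm hidden | 33.3% | 33.3% | 0% |

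Counting alone does almost as well as knowing the sizes, so secrecy about block sizes is not enough while the arms are visible.

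**In patients.** Over 81 assignments, chance gives 81 / 3 = 27 correct guesses. The range 47% to 56% gives 0.47 × 81 ≈ 38 to 0.56 × 81 ≈ 45, that is 11 to 18 more.

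**The case against.** The case on the other side is substantial.

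- **The current patient is concealed.** Release comes through a central system after baseline assessment and confirmed eligibility. This stands. The point concerns later patients only.
- **A guess rate is not a bias.** Bias also needs someone who tracks four strata, favours an arm and influences entry. This stands: no effect on the treatment estimate is shown. Several criteria also leave little to steer. CRS-R stability has a numeric definition, and atrophy and hydrocephalus have numeric limits assessed by two independent neuroradiologists.
- **The result might be a code.** The article does not say so, and it uses the same term for what the therapist receives. If a code is meant, one clarifying sentence settles the matter.
- **Variable blocks still help.** The mixed 4-or-6 scheme, with the spare slot filled at random, is less predictable (50%) than fixed blocks of 6 (54%). Their purpose is weakened, not defeated.

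A reader might also infer three stronger things that the article does not support.

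- *That the coordinator triggers randomisation or screens patients.* The text says only that the coordinator obtains the result.
- *That unblinded staff deal with families.* This requires the coordinator in Follow-up retention strategy to be the same person, which is not stated. Staff are also told not to discuss treatment.
- *That the therapist should not know the arm.* No declared blinding covers the therapist. Real MNS intensity is set from the motor threshold and sham from the sensory threshold, so whoever sets it may need the arm. How this fits with pre-programmed devices is for the authors to reconcile.

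The primary outcome is further protected because the assessors are declared blind.

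**Conclusion.** The point holds in a limited form. The article gives one site role every allocation without a stated need. Anyone holding that record can guess the next arm in about 47% to 56% of cases instead of 33%, a gain of roughly 14 to 23 percentage points. Certain knowledge is rarer, about 2% to 18% of assignments. These figures assume roughly equal strata and a total of 81. The upper and lower ends depend on how the block sizes are read, since blocks of 4 do not fit three arms. They measure an opportunity for selection bias, not its occurrence. Whether the opportunity matters depends on two facts that the article leaves open: whether the coordinator has any part in screening, and whether this person is also the families' contact. The change is worth making because it removes the route whatever the answers are, at almost no cost.

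**What to change.** Amend the randomisation paragraph in Study design along these lines: after eligibility is confirmed, the coordinator receives only confirmation that the patient has been randomised and a randomisation number; the system releases the arm or device code only to the person who sets the stimulators, and that person takes no part in screening, consent or eligibility decisions. Withhold block sizes from site staff. Since the present sizes are printed and a block of 4 does not fit three arms, the sizes have to be reset in any case, and the new ones can be kept in a restricted document. If the allocation result is already a code that does not reveal the arm, say so instead.

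The cost is a permission setting in the existing web system and a short protocol edit, with no extra patients. The small downside is that the coordinator can no longer check device use by arm, so the operator keeps an unblinded log for this. The operator need not be barred from adverse-event inquiry. Observation is planned at every session, and such a bar could require a second person at each one.

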### Experimental group intervention

The experimental group (tDCS+MNS group) will receive tDCS combined with MNS. tDCS will be administered using a Starstim tDCS stimulator (Neuroelectrics, Barcelona, Spain). The anode electrode (5 × 7 cm) will be placed over the left dorsolateral prefrontal cortex (F3 position according to the international 10–20 system), and the cathode electrode (5 × 7 cm) will be placed over the right supraorbital area (Fp2 position). Stimulation will be delivered at 2 mA for 20 min, with ramp-up and ramp-down periods of 30 s each, once daily for 5 consecutive days per week, for 4 weeks. MNS will be administered using a Digitimer DS7A constant current stimulator (Digitimer Ltd., Hertfordshire, UK). Electrodes will be placed on the right median nerve (2 cm proximal to the wrist crease), with intensity set at 300% of the motor threshold, frequency at 10 Hz, pulse width at 1 ms, for a total duration of 120 min. The MNS will begin 10 min before tDCS starts and continue for 90 min after tDCS ends, ensuring a 20-min overlap of both stimulations (30). The combined tDCS and MNS stimulation protocol is shown in Figure 2, which details the stimulation parameters and timing sequence.

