### Control group interventions

Control Group 1 (Sham tDCS+MNS group) will receive sham tDCS combined with MNS treatment. Sham tDCS will ramp up to 2 mA over 30 s, then ramp down to 0 over 30 s, and remain off thereafter (31). MNS parameters will be identical to the experimental group.

Control Group 2 (tDCS+Sham MNS group) will receive sham MNS combined with tDCS treatment. tDCS parameters will be identical to the experimental group, but MNS intensity will be set at 50% of the sensory threshold, insufficient to elicit muscle contraction (20).

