#### Predetermined visit schedule

The visit schedule for all assessments is presented in Table 1. Participants will be evaluated at screening (Week −2), baseline (Week 0), post-treatment (Week 4), and follow-up (Weeks 6, 8, 16, and 28). Demographic characteristics and medical history will be collected only at the first visit. Baseline assessments, including CRS-R, fNIRS, EEG, ERPs, GOS-E, and fMRI, will be conducted at Week 0, followed by randomization and treatment initiation. The primary outcome measure (CRS-R) will be assessed at all visits starting from baseline. Secondary outcome measures will be measured at various time points. All follow-up visits will be conducted in outpatient settings. For patients unable to attend in person, home visits or video follow-ups will be arranged (22).

**Table 1 tab1:** Schedule of enrolment, interventions, and assessments.

	Study Period						
	Screening	Baseline	Treatment	Follow-up			
Week	−2	0	4	6	8	16	28
Enrolment							
Eligibility screen	**×**						
Signed informed consent	**×**						
Allocation		**×**					
Randomization		**×**					
Interventions							
tDCS + MNS group		**×**	**×**				
tDCS sham + MNS group		**×**	**×**				
tDCS + MNS sham group		**×**	**×**				
Assessments							
Primary outcome							
CRS-R		**×**	**×**	**×**	**×**	**×**	**×**
Secondary outcomes							
fNIRS		**×**	**×**				
EEG		**×**	**×**				
ERPs		**×**	**×**				
GOS-E		**×**			**×**	**×**	
fMRI		**×**					**×**
Adverse Events			**×**	**×**	**×**	**×**	**×**

× Represents data collection timepoint. tDCS, transcranial direct current stimulation; MNS, median nerve stimulation; CRS-R, Coma Recovery Scale-Revised; fNIRS, Functional Near-Infrared Spectroscopy; EEG, Electroencephalography; ERPs, Event-Related Potentials; GOS-E, Glasgow Outcome Scale-Extended; fMRI, Functional magnetic resonance imaging.

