#### Study safety

Based on previous research, transcranial direct current stimulation and median nerve stimulation are considered relatively safe, non-invasive techniques (16). However, we will closely monitor potential adverse events, including but not limited to: (1) mild discomfort, redness, or itching at the stimulation site; (2) transient headache or dizziness; (3) nausea; (4) fatigue. To address these potential adverse events, we have developed a detailed response plan: (1) All research personnel will receive training in adverse event identification and management. (2) Given that patients with prolonged disorders of consciousness (pDoC) cannot reliably self-report subjective adverse events, a comprehensive monitoring approach has been implemented, including systematic observation of objective signs (skin reactions, autonomic changes such as heart rate, blood pressure, and sweating, facial expressions, and behavioral responses); physiological parameter monitoring (temperature, blood pressure, and heart rate before and after each session); neurophysiological indicators (EEG changes during treatment and follow-up that may indicate discomfort or adverse responses); caregiver reports (detailed inquiries to family members and caregivers about any unusual behaviors or responses); and clinical judgment (comprehensive assessment by experienced clinicians familiar with detecting subtle signs of discomfort in non-communicative patients). (3) Detailed assessments using the above methods will be conducted before and after each treatment session and at all follow-up visits. (4) Any identified adverse events will be documented and evaluated by a physician not involved in the direct treatment delivery. (5) For adverse events management, we will implement a standardized classification system based on the Common Terminology Criteria for Adverse Events (CTCAE v5.0). All adverse events will be graded on a 5-point scale (1: mild; 2: moderate; 3: severe; 4: life-threatening; 5: death-related) and systematically documented in a dedicated adverse event log. Events of grade 3 or higher will be reported to the ethics committee within 24 h.

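### The non-disclosure rule is addressed to staff and to patients who mostly cannot communicate, while families and caregivers, who could see whether MNS is real, fall under no blinding measure

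*Protocol article*

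**What the plan says.** The Study design section describes the trial as triple-blind: "patients, outcome assessors, and data analysts will be blinded to treatment allocation". To keep the blind it states: "All research personnel and participants will be instructed not to discuss treatment details during the study". It then provides a check: "The effectiveness of blinding will be regularly assessed by asking assessors to guess the type of treatment they evaluated". Patients who regain communication are also asked to guess, but the section concedes that "this will not be possible for patients who remain in pDoC throughout the study".

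The two MNS conditions are set out under the interventions. Real MNS is given "with intensity set at 300% of the motor threshold, frequency at 10 Hz, pulse width at 1 ms, for a total duration of 120 min" (Experimental group intervention). In the sham condition, "MNS intensity will be set at 50% of the sensory threshold, insufficient to elicit muscle contraction" (Control group interventions).

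Families enter in other sections. Study safety lists, among its monitoring methods, "caregiver reports (detailed inquiries to family members and caregivers about any unusual behaviors or responses"), and applies these methods around each treatment session and at every follow-up visit. Predetermined visit schedule places CRS-R at all visits from baseline and adds: "For patients unable to attend in person, home visits or video follow-ups will be arranged".

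**The concern.** An instruction not to discuss treatment protects the blind only if it reaches the people who could break it. Here it reaches staff, and patients of whom most cannot speak. A relative or caregiver at the bedside can both observe and talk, yet is neither listed as blinded nor instructed.

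CRS-R is a behavioural scale scored by an evaluator. If a caregiver mentions that the hand twitched, or never moved, during sessions, the evaluator learns whether MNS was real. Ratings could then lean towards what the evaluator expects of that arm. The contrast most exposed is tDCS+MNS against tDCS+sham MNS, which isolates what MNS adds.

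**Working it through.** The plan gives no figure on this point to reproduce. The check is a comparison of passages, followed by an illustration on assumed values.

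**1. Who is covered by each measure in Study design**

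| Measure | Patients | Assessors | Families, caregivers, representatives |
|---|---|---|---|
| Named as blinded | yes | yes | no |
| Told not to discuss treatment | yes | yes, as research personnel | not named |
| Asked to guess the arm | only if communication returns | yes | no |

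**2. Whether the word participants includes families.** Follow-up retention strategy speaks of contact with the families and caregivers of participants. The discontinuation criteria in Study safety list a request by the participant or by the legal representative as alternatives. Ethical considerations has representatives or relatives consent for participants. In each place the two groups are distinct.

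**3. The visible cue, by arm.** A stimulus above motor threshold is expected to produce a contraction. The sham setting is stated not to.

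| Arm | Contraction expected |
|---|---|
| tDCS+MNS | yes |
| sham tDCS+MNS | yes (same MNS settings) |
| tDCS+sham MNS | no |

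Of the three pairwise comparisons, the two that involve tDCS+sham MNS differ on the cue. The comparison of tDCS+MNS with sham tDCS+MNS does not. Identical devices and electrode positions do not hide a contraction, and the validation cited for sham concerns tDCS and what the recipient can perceive.

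**4. Where caregiver and assessor could meet.** Table 1 marks both CRS-R and adverse events at Weeks 4, 6, 8, 16 and 28. Caregivers are questioned explicitly at all follow-up visits (Weeks 6, 8, 16 and 28), and home or video contact is attached to those visits. The primary outcome is the change from baseline to post-treatment, which is Week 4, so the home and video route does not reach it. Those visits enter through the later time points of the 3 × 6 repeated-measures model. No section says who collects caregiver reports or keeps that person apart from the CRS-R evaluator.

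**5. Illustration only.** Inputs from Sample size: SD 7.3 and 27 per arm. The rating bias b is assumed. The calculation is a simple two-arm normal test, not the planned model.

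SE = SD × √(2/n) = 7.3 × √(2/27) = 1.99.

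Rejection rate with no true effect = 1 − Φ(1.96 − b/SE) + Φ(−1.96 − b/SE).

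| Assumed b (points) | SD 7.3, n = 27 | SD 7.3, n = 22 | SD 5 (assumed), n = 27 |
|---|---|---|---|
| 0.5 | 5.7% | 5.6% | 6.6% |
| 1 | 7.9% | 7.4% | 11.4% |
| 2 | 17.2% | 14.9% | 31.2% |

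Here b is an average over the whole comparison. If a share p of ratings is exposed and each shifts by s points, b = p × s. Assuming p from 0.20 to 0.50 and s from 0.5 to 1.5 gives b from 0.20 × 0.5 = 0.10 to 0.50 × 1.5 = 0.75. That is 2.5% to 18.8% of the 4-point target, and with SD 7.3 the error rate stays below the 7.9% shown for 1 point. None of p, s or b comes from the documents.

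**The case against.** The strongest reply is that this is an omission in a condensed article, and that family instructions belong in the full protocol or the consent material. That would succeed if the article had merely been brief. It was not: it lists the blinded roles, the addressees of the instruction and the people asked to guess, and the addressees it chose are largely unable to act on the instruction.

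A second reply is that participants, in a trial with proxy consent, can only be instructed through their representatives. This is plausible but uncertain, since the article separates the two groups elsewhere.

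Other replies stand in part:

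- Research personnel are already told not to discuss treatment, so a rule against staff revealing the arm to families largely exists.
- Technicians take no part in assessment, and the assessors' guesses may detect a leak. Neither prevents one that starts with a caregiver.
- The leak needs several steps: the caregiver attends, notices the hand, and speaks to the evaluator. The documents state none of these. They also do not exclude them.

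A reader might further infer that adverse-event reporting and retention are biased as well. The documents do not support saying so. Caregiver reports are one of five monitoring sources, a physician outside treatment delivery evaluates events, and a physician not directly involved in delivery takes discontinuation decisions. These are partial safeguards, though a representative's request is itself a ground for stopping.

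**Conclusion.** The concern holds in a limited form. The blinding rules omit the group best placed to see and repeat the MNS cue, and that group is questioned at visits where CRS-R is scored. This leaves the assessor blind exposed for comparisons with tDCS+sham MNS.

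A reader might infer that families can identify all three arms, or that the Week 4 result is compromised through home visits. Neither follows: the cue reveals MNS status only, and home and video contact belongs to follow-up. In-person contact at Week 4 is not excluded, but no text establishes it.

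The size of any bias cannot be estimated from the documents, and the percentages in the illustration show sensitivity to assumed values, not expected inflation. The conclusion rests on two inferences: that contraction under real MNS is visible to someone present, and that some caregivers are present. The gap merits correction because closing it is almost free. It does not show that the trial is unblinded.

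**What to change.** Amend the blinding paragraph of Study design as follows.

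- Add legal representatives, family members and caregivers to the blinded roles, and address the non-disclosure instruction to them as well as to staff and patients.
- Give them one neutral information script, identical in all three arms, saying that hand movement may or may not be seen.
- Have the CRS-R evaluator open each visit, including home and video visits, by asking not to be told about the sessions.
- Record any disclosure on the CRS-R form, so that disclosures can be tabulated by arm and visit beside the assessors' guesses.

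The cost is a short script and one form item, with no added visits or staff. No stimulation parameter or clinical rule changes.
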